## 8 Primary and secondary endpoints

### 8.1 Primary endpoints

Incidence of bacteremia during the first month after surgery

Basis for setting primary endpoints

The onset of bacteremia, a severe infection after liver transplantation, is more likely to occur within one month after surgery (63%) based on the results of previous studies. Since the administered NK cells were confirmed in the recipient's body for up to one month, we chose one month as the period to evaluate the inhibition rate of bacteremia development by NK cell therapy.

### 8.2 Secondary endpoints

① Overall survival (6 months, 1, and 3 years postoperatively)

② adverse event

Type and severity of adverse events that occurred in this clinical study, frequency of occurrence, duration of occurrence, and causal relationship

③ Effect on immune response

Evaluation of donor specific immunoreactivity by CFSE-MLR (1, 2, 3, 4 weeks postoperatively), detection of donor specific antibody (DSA) (annual screening), incidence of rejection, evaluation of NK cell activity in recipient peripheral blood

- ④ Presence and timing of hepatocellular carcinoma recurrence (hepatocellular carcinoma cases only) and De novo carcinogenesis
- ⑤ Incidence of infectious diseases (bacterial infections, cytomegalovirus infections, fungal infections, analysis by genetic polymorphism)

#### Rationale for setting secondary endpoints

In order to re-evaluate the efficacy and safety of this treatment, the following secondary endpoints were included

- ① To evaluate its efficacy in long-term survival after liver transplantation
- ② To re-evaluate the safety of this treatment
- ③ To evaluate the effect of this treatment on the immune system of the recipient
- ④ To evaluate the effect of this treatment on carcinogenesis
- ⑤ To evaluate the effect of this treatment on infections other than bacteremia, and to evaluate the difference in the effect of genetic polymorphisms.

## 9 Observation and inspection items and schedule

### 9.1 Inspection Schedule

The schedule for conducting observations, examinations, and evaluations is shown in Table 1 and Table 2 below. The principal investigator and subcontractors will conduct observations, examinations, etc. according to the schedule. Items that can be conducted by research collaborators, such as subject information (background investigation) and clinical examinations, may be conducted by research collaborators under the supervision of the principal investigator.

**Table 1: Observation and examination schedule (Subject: Recipient)**

| 観察日・
評価日 | 同意
取得          | スクリー
ニング       | 術前
検査          | 登録                | 手術
日 | 細胞
投与日 | 細胞
投与日 | 4
日後  | 5
日後    | 1
週間
後 | 2
週間
後 | 4
週間
後 | 8
週間
後 | 12
週間
後 | 6
か月
後 | 以後
6 力月
毎 3 年
まで |
|-------------|-------------------|-------------------|-------------------|-------------------|---------|-----------|-----------|----------|------------|--------------|--------------|--------------|--------------|---------------|--------------|---------------------------|
| 許容範
囲    | 手術前
4 週間
以内 | 手術前
4 週間
以内 | 手術前
4 週間
以内 | 手術前
4 週間
以内 |         | 投与
前   | 投与
後   | 投与
翌日 | 投与
2 日後 | ±2
日      | ±2
日      | ±1
週      | ±1
週      | ±1
週       | ±8
週      | ±8
週                   |
| 同意
取得    | ○                 |                   |                   |                   |         |           |           |          |            |              |              |              |              |               |              |                           |
| 登録          |                   |                   |                   | ○                 |         |           |           |          |            |              |              |              |              |               |              |                           |
| 被験者
情報   |                   | ○                 |                   |                   | ○       |           |           |          |            |              |              |              |              |               |              |                           |
| 臨床
症状    |                   |                   | ○                 |                   |         | ○         | ○         | ○        | ○          | ○            | ○            | ○            | ○            | ○             | ○            | ○                         |
| バイタル
サイン |                   |                   | ○                 |                   |         | ○         | ○         | ○        | ○          | ○            | ○            | ○            | ○            | ○             | ○            | ○                         |
| 血液
検査    |                   |                   | ○                 |                   |         | ○         | ○         | ○        | ○          | ○            | ○            | ○            | ○            | ○             | ○            | ○                         |
| 尿検査         |                   |                   | ○                 |                   |         | ○         |           | ○        | ○          | ○            | ○            | ○            |              |               |              |                           |
| 胸部Xp        |                   |                   | ○                 |                   |         | ○         |           | ○        | ○          | ○            | ○            | ○            |              |               |              |                           |
| 培養          |                   |                   | ○                 |                   |         |           |           |          |            | ○            | ○            | ○            |              |               |              |                           |
| CT          |                   |                   | ○                 |                   |         |           |           |          |            |              |              | ○            |              | ○             | ○            | ○                         |
| フロー
サイト  |                   |                   | ○                 |                   |         | ○         |           |          |            | ○            | ○            | ○            |              |               |              |                           |
| MLR         |                   |                   | ○                 |                   |         |           |           |          |            | ○            | ○            | ○            |              |               |              |                           |
| 有害
事象    |                   |                   |                   |                   |         |           | ○         | ○        | ○          | ○            | ○            | ○            | ○            | ○             | ○            | ○                         |
| 併用
治療    |                   |                   |                   |                   |         |           | ○         | ○        | ○          | ○            | ○            | ○            | ○            | ○             | ○            | ○                         |

**Table 2: Observation and Inspection Schedule (Subject: Donor)**

| Date of observation and evaluation            | Obtaining Consent         | preoperative scan | Registration | procedure |
|-----------------------------------------------|---------------------------|-------------------|--------------|-----------|
| tolerance level                               | Within 4 weeks of surgery |                   |              |           |
| Obtaining Consent                             | p-sound                   |                   |              |           |
| Subject information *                         |                           | p-sound           |              |           |
| clinical condition (of a patient's illness) * |                           | p-sound           |              |           |
| vital signs *                                 |                           | p-sound           |              |           |
| blood test *                                  |                           | p-sound           |              |           |
| Collection of donor graft liver perfusion     |                           |                   |              | p-sound   |

\*: If the patient has been observed within 3 months prior to surgery to confirm the suitability for living donor liver transplantation, the observation and examination data will be used.

## 9.2 Observation and inspection items

In this study, the donor (the cell donor) and the recipient (the recipient to whom the specific cell product will be administered) are the subjects. However, since the purpose of this study is to evaluate the efficacy and safety of the administration of the specific cell product in the recipient, the recipient is the one who will be measured in the observation and inspection items unless otherwise specified. Subjects.

### 9.2.1 screening test

After written consent is obtained, observations and examinations will be conducted for the following items.

- ① Subject information: Subject background (date of birth, gender, height, weight, preoperative status, primary disease, ascites, encephalopathy, preoperative dialysis, preoperative desensitization), current medical history, previous medical history, treatment history for infectious diseases (specific

treatment), treatment history for hepatocellular carcinoma (hepatocellular carcinoma cases only)

### 9.2.2 preoperative scan

- ① Clinical manifestations: symptoms of infection, presence of treatment for infection, other clinical manifestations
- ② Vital signs: blood pressure, pulse rate, body temperature
- ③ Blood test
  - <Hematological tests
    - Red blood cell count, white blood cell count, neutrophil count, lymphocyte count, hemoglobin count, hematocrit count, platelet count
  - Biochemical tests
    - Total bilirubin, Indirect bilirubin, ALB, AST, ALT,  $\gamma$ GTP, ALPH, CRP, BUN, Cre, Na, K, Cl, IgG, IgM, PT, PT-INR, AFP, L3 fraction, PIVKA-II, HBsAg, HBsAb, HBV-DNA, HCV, HCV-RNA, CMV-, IgG, CMV-IgM, EBV-IgG, EBV-IgM, -D glucan, MELD score, Child-Pugh classification IgG, CMV-IgM, EBV-IgG, EBV-IgM,  $\beta$ -D glucan, MELD score, Child-Pugh classification
- ④ Laboratory tests
  - Urinalysis: protein qualitative, sugar qualitative, occult blood qualitative
  - Blood type, HLA
- ⑤ Diagnostic imaging (number of tumors, maximum tumor diameter, localization)
  - Chest X-ray: preoperative diagnosis of hepatocellular carcinoma (hepatocellular carcinoma cases only)
  - Contrast-enhanced CT (MRI or US can be substituted in case of contrast media allergy or renal failure)
- ⑥ Culture test (bacteria species): nasal, urine
  - Criteria for submission of blood cultures (clinically suspicious findings of bacteremia): fever of 38° C or higher, chills, hypotension, clinical symptoms, two sets of blood cultures must be submitted.(Horan, Andrus, & Dudeck, Am J Infect Control, 36,p.309, 2008)
- ⑦ Immunological analysis
  - Peripheral blood flow cytometry (phenotyping): T cell %, NKT cell %, NK cell %, CD69 on NK cell, TRAIL on NK cell, NKp44 on NK cell, NKp46 on NK cell, cytotoxicity test

MLR (lymphocyte mixture test): CD4 T cell SI, CD8 T cell SI, CD4+CD25+T cell %, CD8+CD25+T cell %.

- ⑧ Cell donor information: date of birth, sex, relationship, height, weight, blood type, HLA, CMV-IgM, CMV-IgG, EBV-IgG, EBV-IgM, HBs-Ag, HBs-Ab, HBc-Ab, HCV-Ab, HIV-Ab, (for HBV, HCV, and HIV, the window (HBV, HCV, and HIV should be retested around 3 months after surgery due to the possibility of false negative results due to the window period).

[Observation period; from the time of donor's consent to the date of liver transplantation.]

### 9.2.3 Registration

Based on the results of screening and preoperative laboratory tests, subjects who meet all of the selection criteria at the time of enrollment as specified in "Target Diseases and Eligibility Criteria" and do not meet any of the exclusion criteria will be enrolled.

### 9.2.4 operating day

- ① Surgical information: graft type, graft weight, GRWR, total ischemia time, operation time, blood loss, blood transfusion volume
- ② Liver pathological findings: pathological Milan criteria (only for cases with liver cancer complications), background liver HIA score
- ③ Information on administered cells: collection of liver perfusate, culture of liver-derived lymphocytes, and liver perfusate flow cytometry

### 9.2.5 Day of NK cell administration (postoperative day 3)

[Before NK cell administration]

- ① Clinical manifestations: symptoms of infection, presence of treatment for infection, other clinical manifestations
- ② Vital signs: blood pressure, pulse rate, body temperature
- ③ Blood test

<Hematological examination>: Same as preoperative examination

Biochemical tests

Total bilirubin, Direct bilirubin, ALB, AST, ALT, γGTP, ALPH, CRP, BUN, Cre, Na, K, Cl, PT, IgG, IgM, CNI blood levels

- ④ Urinalysis: protein qualitative, sugar qualitative, occult blood qualitative
- ⑤ Immunological analysis

Peripheral blood flow cytometry (phenotyping): T cell %, NKT cell %, NK cell %, CD69 on NK cell, TRAIL on NK cell, NKp44 on NK cell, NKp46 on NK cell, cytotoxicity test

⑥ Diagnostic imaging: simple chest x-ray

[After NK cell administration.]

① Clinical manifestations: symptoms of infection, presence of treatment for infection, other clinical manifestations

② Vital signs: blood pressure, pulse rate, body temperature

③ Blood test

<Hematological examination>: Same as preoperative examination

Biochemical tests

Total bilirubin, Direct bilirubin, ALB, AST, ALT,  $\gamma$ GTP, ALPH, CRP, BUN, Cre, Na, K, Cl, PT

④ Observation of adverse events

Adverse event name, date of occurrence, grade, severity, treatment, outcome/decision date, causal relationship, comments (details of decision to continue, causal relationship, course, etc.)

The name of the adverse event should be recorded by the diagnosis. The name of the adverse event should be recorded with the name of the diagnosis. However, symptoms and signs that cannot be given a diagnosis should be recorded with the name of the symptom or sign.

Check for infections, use of antibiotics, and rejection.

Patient outcomes (presence/absence of graft failure, presence/absence of death, cause of death), secondary transplantation (presence/absence, timing)

⑤ Confirmation of concomitant treatment: treatment for infections (including prophylactic and anticipatory, therapeutic agent, dose, duration)

#### 9.2.6 1 or 2 days after NK cell administration (postoperative day 4 or 5)

① Clinical manifestations: symptoms of infection, presence of treatment for infection, other clinical manifestations

② Vital signs: blood pressure, pulse rate, body temperature

③ Blood tests

Hematological examination: Same as preoperative examination

Biochemical tests: Same as before NK cell administration on the day of NK cell administration (postoperative day 3)

- ④ Urinalysis: protein qualitative, sugar qualitative, occult blood qualitative
- ⑤ Diagnostic imaging: simple chest x-ray
- ⑥ Observation of adverse events
- ⑦ Confirmation of concomitant treatment

#### 9.2.7 1, 2 weeks after NK cell administration

- ① Clinical manifestations: symptoms of infection, presence of treatment for infection, other clinical manifestations
- ② Vital signs: blood pressure, pulse rate, body temperature
- ③ Blood test

<Hematological examination>: Same as preoperative examination

Biochemical tests

Total bilirubin, Direct bilirubin, ALB, AST, ALT,  $\gamma$ GTP, ALPH, CRP, BUN, Cre, Na, K, Cl, PT, IgG, IgM,  $\beta$ -D glucan, C7-HRP, CNI blood levels

- ④ Urinalysis: protein qualitative, sugar qualitative, occult blood qualitative
- ⑤ Diagnostic imaging: simple chest x-ray
- ⑥ Culture tests (bacterial species): blood, sputum, urine, bile, drains
- ⑦ Immunological analysis

Peripheral blood flow cytometry (phenotyping): T cell %, NKT cell %, NK cell %, CD69 on NK cell, TRAIL on NK cell, NKp44 on NK cell, NKp46 on NK cell, cytotoxicity test

MLR (lymphocyte mixture test): CD4 T cell SI, CD8 T cell SI, CD4+CD25+T cell %, CD8+CD25+T cell %.

- ⑧ Observation of adverse events
- ⑨ Confirmation of concomitant treatment

#### 9.2.8 4 weeks after NK cell administration

- ① Clinical manifestations: symptoms of infection, presence of treatment for infection, other clinical manifestations
- ② Vital signs: blood pressure, pulse rate, body temperature
- ③ Blood test

<Hematological examination>: Same as preoperative examination

Biochemical tests: Same as 1 and 2 weeks after NK cell administration

- ④ Urinalysis: protein qualitative, sugar qualitative, occult blood qualitative

- ⑤ Diagnostic imaging: simple chest X-ray imaging, contrast-enhanced CT (MRI or US can be substituted in case of contrast agent allergy or renal failure)
- ⑥ Culture tests (bacterial species): blood, sputum, urine, bile, drains
- ⑦ Immunological analysis  
Peripheral blood flow cytometry (phenotyping): T cell %, NKT cell %, NK cell %, CD69 on NK cell, TRAIL on NK cell, NKp44 on NK cell, NKp46 on NK cell, cytotoxicity test  
MLR (lymphocyte mixture test): CD4 T cell SI, CD8 T cell SI, CD4+CD25+T cell %, CD8+CD25+T cell %.
- ⑧ Observation of adverse events
- ⑨ Confirmation of concomitant treatment

#### 9.2.9 After 8 weeks and 12 weeks of NK cell administration

- ① Clinical manifestations: symptoms of infection, presence of treatment for infection, other clinical manifestations
- ② Vital signs: blood pressure, pulse rate, body temperature
- ③ Blood test  
<Hematological examination>: Same as preoperative examination  
Biochemical tests: Same as 1 and 2 weeks after NK cell administration
- ④ Observation of adverse events
- ⑤ Confirmation of concomitant treatment

#### 9.2.10 6 months after NK cell administration, then every 6 months for 3 years

- ① Clinical manifestations: symptoms of infection, presence of treatment for infection, other clinical manifestations
- ② Vital signs: blood pressure, pulse rate, body temperature
- ③ Blood test  
<Hematological examination>: Same as preoperative examination  
Biochemical tests  
Total bilirubin, direct bilirubin, ALB, AST, ALT,  $\gamma$ GTP, ALPH, CRP, BUN, Cre, Na, K, Cl, PT, CNI blood levels
- ④ Diagnostic imaging: contrast-enhanced CT (MRI or US can be substituted in case of contrast agent allergy or renal failure)
- ⑤ Observation of adverse events
- ⑥ Confirmation of concomitant treatment

### 9.2.11 when suspended

- ① Reason for discontinuation
- ② Comment.

## 10 Ensuring the safety of subjects

### 10.1 basic facts

In order to ensure the safety of human subjects, principal investigators and sub-investigators shall comply with the following basic items

1. The principal investigator or sub-investigator shall comply with the selection and exclusion criteria for subjects.
2. When a subject receives treatment from a physician other than the principal investigator and sub-investigator of this clinical research, the subject shall notify the physician of his or her participation in this clinical research and the nature of this research.
3. After the completion of this clinical study, patients will be examined for as long as possible and attention will be paid to the occurrence of adverse events.
4. If subjects feel any abnormality in their health, they will be instructed to immediately contact the principal investigator or sub-investigator.
5. When the principal investigator or sub-investigator recognizes that an adverse event has occurred in a subject and that treatment is necessary, the principal investigator or sub-investigator should inform the patient concerned, provide appropriate medical care, and describe the event without discrepancy in the case report form.
6. The principal investigator shall summarize the occurrence of adverse events in a status report and submit it to the Hiroshima University Committee on Regenerative Medicine once a year, and report it to the administrator.

### 10.2 Definition of Adverse Events

An "adverse event" is any unwanted or unintended sign (including abnormal changes in general laboratory values), symptom, or illness that occurs while a subject is participating in a clinical study, whether or not causally related to the protocol treatment. Clinically significant worsening of symptoms that were present prior to protocol treatment is also an adverse event. Physiological changes that are not considered clinically objectionable in terms of frequency or degree are not considered adverse events.

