|                                                    | 
On the third day of culture, the cell suspension is centrifuged and washed with saline. Check the number of cells and viability after culture. At this time, the cell status, sterility test by Gram staining, endotoxin test, mycoplasma negative test, and bacterial culture test are performed. Suspend the cell suspension to be administered in albumin-containing saline.
 
4 . Cell shipment
The clinical research manager and the quality manager shall make the shipping judgment of the test article. For the infection test, the results of endotoxin test and bacterial culture test at the start of culture, as well as the results of cell condition and Gram stained sterility test method at the time of cell collection shall be used for the shipment judgment.
 
5 . Cell administration
On the third postoperative day after liver transplantation, with the permission of the recipient's primary physician, cell suspension is administered to the liver transplant recipient intravenously over a period of 30 minutes to 1 hour. The cells are administered only once, on the third postoperative day.
 |
| Concomitant use of prohibited drugs and therapies  | None in particular                                                                                                                                                                                                                                                                                                                                                                                                                                                                                                                                                                                                                                                                                                                                                                                                                                                                                                                                                                                                                                                                                                                                      |

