# 1 Research Objectives

The purpose of this clinical study was to evaluate whether immunostimulatory therapy using activated natural killer (NK) cells derived from liver donor on day 3 after living donor partial liver transplantation can reduce the incidence of severe infections after liver transplantation in patients with uncompensated cirrhosis for whom no other treatment is available. This is an open-label study to compare the results. In this study, we will investigate the frequency of bloodstream infection (bacteremia) after liver transplantation and the safety of NK cell administration.

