## 7.4 Protocol Treatment Plan

### 7.4.1 Definition of Protocol Treatment

Lymphocyte fractions are extracted from donor graft liver perfusion effluent collected at the time of living partial liver transplantation surgery by the specific gravity centrifugation method. The liver-derived lymphocytes are cultured in complete medium with IL-2 (100 IU/ml) and donor plasma (final concentration 2%) for 3 days. One day prior to administration, anti-CD3 antibody (1 µg/ml) is added to the medium to remove CD3 positive T cells. The cell suspension is collected, centrifuged, and washed with saline, and then the cells are suspended in albumin-containing saline and administered as a single dose to the liver transplant recipient

transvenously on postoperative day 3. Protocol treatment is defined as from donor graft liver perfusion to the completion of donor liver-derived activated NK cell administration.

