### 10.3 Assessment of adverse events

Adverse events observed during the conduct of clinical research will be evaluated according to the schedule specified in "Observation and Examination Items and Schedule".

The severity of adverse events will be determined based on the NCI-Common Terminology Criteria for Adverse Events (NCI-CTC-AE Ver4.0 Japanese version).

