## 15.6 Safety analysis

### *adverse event*

The number of cases, number of incidences, and percentage of incidences of adverse events will be tabulated by event and by severity. The number of cases, number of incidences, and percentage of incidences of adverse events by event type and severity will also be tabulated.

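### The safety reference state lies before the transplant but adverse events are observed only after the day-3 infusion, so the safety summaries mix surgical effects with any effect of the cells

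*Protocol*

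**What the plan says.** Part of the objective in Protocol section 1 is "the safety of NK cell administration". The cells are given after the operation: "The cells are administered only once, on the third postoperative day" (section 0).

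Four places in the protocol fix how safety is measured.

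- **Definition (10.2).** An adverse event is any unwanted sign, including abnormal laboratory change, "symptom, or illness that occurs while a subject is participating in a clinical study, whether or not causally related to the protocol treatment". The section continues: "Clinically significant worsening of symptoms that were present prior to protocol treatment is also an adverse event".
- **Start of treatment (7.4.1).** "Protocol treatment is defined as from donor graft liver perfusion to the completion of donor liver-derived activated NK cell administration".
- **Collection (10.3, Table 1, 9.2.5).** "Adverse events observed during the conduct of clinical research will be evaluated according to the schedule specified in" the observation schedule. In Table 1 the adverse-event row has its first mark in the column after administration. In 9.2.5, "Observation of adverse events" appears only in the block after administration, with date of occurrence, grade and causal relationship among the items recorded.
- **Analysis (15.6).** "The number of cases, number of incidences, and percentage of incidences of adverse events will be tabulated by event and by severity". For vital signs and laboratory tests, change is calculated from the preoperative examination, which is named as baseline.

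Section 9.2.5 also schedules an examination on day 3 before the infusion, with clinical findings, vital signs, haematology and biochemistry. No summary in 15.6 uses it as the reference.

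**The concern.** The question for safety is what happens to a recipient after the cells are given. The protocol's reference state is that of the same patient before a liver transplant. Between the two lie a major operation and three days of early postoperative care. In a randomised study a control group would carry the same surgical background, and it could be subtracted. Section 7.1 describes a single-centre open-label study with historical data as control, so no concurrent group can do this.

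The definition and the collection schedule also start at different times. The definition runs from participation; observation runs from the end of the infusion. Nothing in 15.6 says which governs an abnormality already present when the infusion begins, or whether one that came and went before the infusion belongs in the tables. At stake is how clearly the safety results can be read, which is one of the study's two stated aims.

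**Working it through.** The protocol states no figure that this point depends on, so the check sets the passages side by side.

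**Step 1: the time points**

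| Element | Source | Time relative to infusion |
|---|---|---|
| Event definition | 10.2 | from participation; no limit at the infusion |
| Reference for worsening | 10.2 with 7.4.1 | before graft perfusion, about 3 days earlier |
| Baseline for laboratory and vital-sign change | 15.6, 15.4 | last preoperative value |
| First adverse-event observation | 10.3, Table 1, 9.2.5 | after the infusion, day 3 |
| Pre-infusion examination | 9.2.5 | immediately before, day 3 |

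Table 1 allows the preoperative examination up to 4 weeks before surgery, and 15.4 takes the value nearest to surgery. The baseline therefore lies between 3 days and 28 + 3 = 31 days before the infusion. In every case the operation falls in between.

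**Step 2: three hypothetical recipients**

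- *A.* Transaminase is normal before surgery, grade 3 before the infusion, and lower but still grade 3 on day 4. It is an abnormal laboratory change during participation and is present at a scheduled observation. If it is recorded as an event, it enters the table at grade 3, although the value improved after the infusion.
- *B.* Platelets are grade 2 before surgery, grade 3 before the infusion and unchanged on day 4. The worsening sentence in 10.2 speaks of symptoms, but its first sentence includes laboratory change. This too can enter at grade 3 with nothing altered after the cells.
- *C.* A severe event on day 1 resolves before the infusion. It meets 10.2, but no adverse-event observation is scheduled while it is present. Whether it is recorded depends on which passage the staff follow.

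**Step 3: the change summaries**

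Within one patient, with all values taken from the same test:

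(post-infusion − preoperative) = (pre-infusion − preoperative) + (post-infusion − pre-infusion)

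Section 15.6 summarises the left side. The first term on the right is surgery and early recovery. Only the second term covers the period after the cells. If the day-3 pre-infusion value is itself summarised as a postoperative time point, the mean of the second term can be recovered by subtraction, provided the same patients have both values. Its standard deviation, median and quartiles cannot be recovered from the separate summaries.

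**Step 4: the size**

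The number of the 37 planned recipients affected is 37 times the share who carry a clinically significant abnormality through the infusion. The documents do not give that share, and I have not assumed one.

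**The case against.** The strongest reply is that the schedule is itself an onset limit: 10.3 ties evaluation to it, and it begins after the infusion. This stands for recipient C, and it rules out saying that all pre-infusion abnormalities are counted. It does not settle A or B, whose abnormalities are present at the post-infusion visits.

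Second, 10.2 leaves out physiological changes judged not clinically objectionable. This will remove some carry-over. It depends on judgement, names no pre-infusion reference and does not clearly cover grade 3 values.

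Third, a reader might infer that the tables charge surgical events to the cells. They do not. Section 10.2 counts events whatever their cause, 9.2.5 records causal relationship for each, 8.2 makes it part of the endpoint, and the interim safety trigger in 7.5 uses only events for which a causal link to the cells cannot be excluded.

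Fourth, a reader might infer that an infusion signal would be hidden altogether. The documents do not support this either. Tables by event keep transaminase and platelet rows apart from rows for chills or rash. Mixing occurs within a row, for events that can arise from both surgery and infusion. Fever, seen in 3 of 24 patients in the earlier cohort (10.4.1), is a plausible example.

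Fifth, an onset flag, a separate listing and a causality table are details commonly left to the SAP, which is not shown. The missing causality table is no finding in itself, and the near-repeated sentence in 15.6 may reflect text lost in translation. What the protocol does fix is the reference state, the preoperative baseline and the start of observation. Those do not fit together, and an SAP cannot recover events that were never scheduled for collection.

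**Conclusion.** The point holds in a limited form. The protocol places its safety reference before the transplant and starts observing adverse events after the infusion. Transplant-related abnormalities that persist to the post-infusion visits can therefore enter the adverse-event tables at full grade. The laboratory and vital-sign summaries combine surgery with any effect of the cells. Events that resolve before the infusion fall between the definition and the schedule.

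The size cannot be given as a count, because the documents report no rate of abnormality on day 3 before infusion. What can be stated is the misplacement of the reference: 3 to about 31 days before the cells, with the operation always in between. The conclusion assumes that some abnormalities caused by the operation are still present at the first post-infusion visits and are judged clinically significant.

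The primary endpoint, the sample size and the causality-limited interim trigger do not depend on this point. It concerns how readily the safety results can be interpreted.

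**What to change.** Reconcile 7.4.1, 9.2.5, 10.2, 10.3, Table 1 and 15.6, and state whether events between surgery and infusion are to be collected. In 15.6:

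- Tabulate adverse events with onset, or an increase in CTCAE grade, after the start of the NK infusion, using the day-3 pre-infusion examination in 9.2.5 as reference.
- List events with earlier onset separately.
- Show laboratory and vital-sign change from the day-3 pre-infusion value beside the change from the preoperative value.
- Optionally add a table by causal relationship, which 8.2 already names.

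The cost is a few sentences, one derived flag and some extra tables. Grade, date of occurrence and the pre-infusion values are already collected. For an event dated on day 3 itself the date alone does not show whether it began before or after the infusion, so the flag must rest on the pre-infusion findings or a before/after mark on the case report form. The downside is that events that begin before the infusion and do not worsen move out of the main table. The separate listing keeps them visible.
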